# research design and methods

## Overview

1. Study Setting: Umlazi/Philasande Research Clinic and Gateway Umlazi Clinic
2. Study Design: This study is a prospective two-arm, quasi-experimental design comparing a primary health care intervention plan with usual care.
3. Target Population: HIV infected women attending PHC
4. Study population: HIV infected women aged from 18 to 49 years of age and receiving HIV care at PHC clinics.
5. Inclusion criteria

- HIV infected women
- On ART for at least 1 year
- Equal to/older than 18 years of age
- Equal to/younger than 49 years of age
- Plans to remain in the study catchment area for at least 3 years

1. Exclusion criteria

- Participant declines study participation

1. Sampling

• Size of sample

400 HIV-infected women consisting of an intervention arm of 200 women co-enrolled in the PROMOTE study at the Umlazi CRS (see method of sampling for details), and a control arm of 200 women receiving HIV care at the PHC. With a 20-30% estimated prevalence of metabolic syndrome in people living with HIV without any specific intervention in the risk factor modification of cardiovascular disease and a proposed 10-15% estimated incidence of metabolic syndrome in the intervention arm, 132 participants per arm would allow for 80% power. An additional 10% can be added to allow for loss to follow-up. The larger proposed sample size will allow for external validity / generalizability.

- Method of selecting sample

Two HIV-infected female cohorts will be matched for receipt of ART duration >1 year and for age will be compared in the study. Method of selection will be via convenience sampling.

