**Intervention group**: There are 245 HIV infected women between 18 and 49 years of age, who have been on ART for more than 1 year and attending the CAPRISA Research Clinic in Umlazi. These women were enrolled into the PEPFAR PROMise Ongoing Treatment Evaluation (PROMOTE) observational study from May-June 2017. This study has been implemented to provide long-term follow-up data on safety outcomes of widespread use of combination antiretrovirals (cART) among an already well-characterized cohort of HIV infected mothers and their children who previously enrolled in the multi-site PROMISE study. This cohort was selected for the proposed intervention arm because the principal investigator is based at the research clinic. Women will be briefed at their next PROMOTE study visit and the 1^st^ 200 interested candidates meeting all eligibility criteria will be co-enrolled into the Intervention arm of the Sub-study.

**Control group**: The Tier data base will be used to select HIV infected women aged between 18-49 years, receiving ART for more than 1 year at the Umlazi Gateway PHC. Scheduled clinic visits at similar time points to the anticipated clinic visits in the intervention group will be used to establish a list of potentially eligible women. Following a matched pool of data, the first 200 women fulfilling the inclusion criteria, who attend the clinic for their next appointment and who consent to study participation will be enrolled.

1. Data sources

- Intervention group: Each participant in the intervention group will be assigned a new Participant identifier number (PID) in addition to the PROMOTE PID. History taking and physical exam, as well as laboratory results and where applicable ultrasound reports, will be entered directly into a data collection tool on a Microsoft Excel spreadsheet (Appendix I).
- Control group: Participants will be assigned a PID in addition to their clinic chart number. Information from clinic patient medical records will be entered directly into the data collection tool (Appendix II). At the final study visit; history, physical exam, lab report finding and ultrasound findings (where applicable), will be source documented.

1. Measures to ensure validity

- Internal
- The prospective nature of the study, large sample size, careful matching between cohorts by age category and by duration of ART aims to counteract the potential for selection bias.

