- **Intervention group**: The prevalence of CVD risk factors will be determined by data collection through history taking, physical examination, and laboratory and radiology investigations as per the data collection tool. CVD risk assessment will be performed annually using a combination of the WHO and International Society of Hypertension cardiovascular risk prediction (WHO/ISH) and the DAD CHD equation. The intervention proposed is a modified WHO PEN algorithm incorporated into HIV management guidelines at study entry. Trends in all risk factors will be monitored, and new risk factors identified, with 6 monthly intervention during the first year, and annually for three years thereafter.
- **Control group**: Following informed consent, data will be collected from the participants ARV clinic medical chart as per the data collection tool. Standard of care HIV management and primary health care will be provided by public sector clinic staff according to current national guidelines. No study investigations or study questionnaires will be carried out at entry visit until the final study visit. There will be regular telephonic follow up with the participants to maintain study retention. Chart review data collection at 6 monthly intervals. CVD risk factors, as per outcomes described above, will be measured by the study at a single 3 year final study visit. Information obtained will be conveyed to the clinic staff for further management if required.

1. Plan for Data handling/processing

- Data will be analysed using SAS or SPSS software

1. Statistical methods

- Descriptive statistics-continuous variables will be represented by means, medians, prevalence, standard deviation.

The categorical variables will be represented by N+%

- Analytic statistics

The continuous variables will be compared by use of t-tests or Wilcoxon rank sum tests.

The categorical variables will be compared using Chi sq or Fisher’s exact test/

- Logistic regression will be applied to identify predictors of cardiovascular disease between the two arms, and between those participants who exhibit atherosclerosis by carotid intima thickness and those who don’t.

1. List of possible confounders

- Women in the intervention group are already enrolled in a study with controlled settings. These women may have commenced ART with a higher baseline CD4 counts.
- Multivariate logression analyses will be utilized in order to control for confounders.

1. List of associations to be measured

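### With one clinic per arm, the planned tests and the stated 80% power describe a difference between two clinics; matching and regression cannot separate clinic from intervention

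*Protocol*

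**What the plan says.** All of this is in the Protocol, Research design and methods, Overview.

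- **Setting.** Two sites are named: "Umlazi/Philasande Research Clinic and Gateway Umlazi Clinic".
- **Intervention arm.** It is drawn from 245 women "who have been on ART for more than 1 year and attending the CAPRISA Research Clinic in Umlazi"; the first 200 who are interested and eligible are co-enrolled. The reason given is: "This cohort was selected for the proposed intervention arm because the principal investigator is based at the research clinic".
- **Control arm.** It is drawn from women "receiving ART for more than 1 year at the Umlazi Gateway PHC".
- **Sample size.** With 20-30% metabolic syndrome expected without intervention and 10-15% with it, "132 participants per arm would allow for 80% power". Planned enrolment is 200 per arm. The significance level, the pair of rates used and an ICC are not stated.
- **Statistical methods.** "The continuous variables will be compared by use of t-tests or Wilcoxon rank sum tests". For categories: "The categorical variables will be compared using Chi sq or" Fisher's exact test.
- **Protection against bias.** Selection is by convenience sampling with matching on age and ART duration, and multivariable regression is planned for confounders. The protocol lists as a possible confounder that intervention women already belong to a study with controlled settings. It also counts the large sample among the measures against selection bias, and says the larger sample supports generalizability.

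The first primary objective, under Specific Objectives, is the effectiveness of WHO PEN in identifying and modifying risk factors.

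**The concern.** The tests ask whether women at the two clinics could come from one distribution. The objective asks whether WHO PEN has an effect. These are the same question only if two clinics giving the same care would produce the same results apart from sampling of women. Staffing, visit schedules, who attends, and other features of a research clinic and a public clinic can make them differ, and such a difference would be read as intervention effect.

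Adding women does not help. It narrows the sampling error around each clinic's own level but leaves the difference between the levels untouched, so the naive test rejects more often for clinic differences alone. At stake are the error rate behind any effectiveness claim and the meaning of the power statement.

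**Working it through.** **Inputs from the protocol:** one clinic per arm; 132 per arm for 80% power; 200 per arm planned; control rate 20-30%, intervention rate 10-15%. **Assumed:** two-sided 5% level; ICC of 0.005, 0.01 and 0.02.

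**1. The plan's own figure.** Take 30% v 15%, mean 22.5%, difference 0.15.

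n0 = [1.96·√(2·0.225·0.775) + 0.8416·√(0.3·0.7 + 0.15·0.85)]² / 0.15² = 120.5

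With continuity correction: n = (n0/4)·[1 + √(1 + 4/(n0·0.15))]² = 133.5, so 134, within 2% of 132. No other pair from the ends and midpoints of the two ranges gave a figure close to 132 under two-sided testing. The formula takes the women as independent and has no clinic term.

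**2. Other rates, still with no clinic variation.** At 132 per arm without continuity correction, power is about 84% for 30% v 15% (unpooled variance; 83.5% pooled). For 20% v 10% it is about 63%, and 199 per arm would be needed for 80%. Wider gaps, such as 30% v 10%, give more than 80%.

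**3. Degrees of freedom.** Between-clinic degrees of freedom are 2·(1 − 1) = 0. The ICC cannot be estimated from these data, and a clinic term in a regression would be the arm term.

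**4. False-positive rate of the unadjusted test.** With design effect DE = 1 + (n − 1)·ICC, the true rejection rate is 2·[1 − Φ(1.96/√DE)].

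**5. Power for 30% v 15% with the ICC treated as known.** v = 0.21 + 0.1275 = 0.3375; SE = √(v·DE/n); power = Φ(0.15/SE − 1.96).

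| ICC | n per arm | DE | False-positive rate | Power |
|---|---|---|---|---|
| 0 | 132 | 1.00 | 5.0% | 84% |
| 0.005 | 132 | 1.66 | 12.8% | 64% |
| 0.01 | 132 | 2.31 | 19.7% | 50% |
| 0.02 | 132 | 3.62 | 30.3% | 34% |
| 0 | 200 | 1.00 | 5.0% | 95% |
| 0.005 | 200 | 2.00 | 16.5% | 73% |
| 0.01 | 200 | 2.99 | 25.7% | 56% |
| 0.02 | 200 | 4.98 | 38.0% | 37% |

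A pooled null variance lowers the powers at non-zero ICC by one to two points.

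**6. Where 80% is lost.** For 30% v 15%, power falls below 80% at an ICC of about 0.0007 to 0.0009 at 132 per arm (pooled or unpooled variance), and just above 0.003 at 200.

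**7. Scale.** At a rate of 22.5%, an ICC of 0.01 means true clinic rates vary with a standard deviation of √(0.01·0.225·0.775) = 0.042, about 4 percentage points. At that ICC, power cannot exceed Φ(0.15/√(0.01·0.3375) − 1.96) = 73% with any number of women.

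**The case against.** The strongest reply is that this is mainly confounding by setting, not a cluster problem. Women consent individually, 200 of 245 enrol, and the lifestyle advice is given to individuals. The two clinics are not random draws from a population of clinics, so an ICC is an imperfect model for a systematic difference of unknown sign. The protocol calls the design quasi-experimental and names the controlled study setting as a possible confounder. It plans matching and multivariable regression. The control arm's final-visit risk factors are measured by the study, and samples go to a certified laboratory, so differences in routine clinic measurement matter less at that visit.

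Much of this stands. A reader might infer that a whole clinic was allocated as a cluster; the enrolment text does not say so. A reader might also infer that t-tests or chi-square tests are the wrong tests for these variables, or that nothing is done about case mix. Neither follows: the tests suit a comparison of two groups of women, and adjustment is planned.

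What does not stand is that these measures rescue the effectiveness reading. Matching and regression act on participant covariates, and naming the setting as a confounder does not make it adjustable when it coincides with arm. Nor is this a detail for a statistical analysis plan: the clinics, the allocation, the tests and the power are fixed in the protocol, and no later analysis can supply the missing degrees of freedom.

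**Conclusion.** The point holds in a limited form. Clinic and intervention are inseparable in this design, and the 80% power is the power to detect a difference between two clinics, for 30% v 15%, with no clinic variation.

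Over ICCs of 0.005 to 0.02, the false-positive rate of a nominal 5% unadjusted test is about 13% to 30% at 132 per arm and 17% to 38% at 200. Power for 30% v 15% is about 64% down to 34% at 132, and 73% down to 37% at 200.

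These sizes rest on assumed ICCs that the protocol does not give and the design cannot estimate. The powers describe a test that could be run only with an ICC supplied from outside. The error rates apply to the unadjusted tests; covariate adjustment may reduce the part of a clinic difference that comes from measured case mix, by an unknown amount.

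A reader might conclude that 80% power exists only if clinics never differ. That is nearly true at 132 per arm but too strong for the planned sample: at 200 per arm and 30% v 15%, power stays above 80% to an ICC of about 0.003. Conversely, absence of clinic variation is not enough if the rates are 20% v 10%, where 132 per arm gives about 63%.

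**What to change.** - **Sampling (size of sample).** State that the 80% power is for 30% v 15%, assumes no between-clinic variation, and refers to detecting a difference between two clinics. Add the values at 132 and 200 per arm over the assumed ICC range, labelled as assumptions.
- **Statistical methods.** Describe the arm comparison as a two-clinic comparison, reported as adjusted estimates with intervals. State that a difference will not be attributed to WHO PEN on a significance test alone.
- **Any ICC-inflated interval.** Mark it as illustrative. It widens the interval around the estimate but does not correct bias from systematic differences between the research clinic and the public clinic.
- **Sampling and Measures to ensure validity.** Remove the claims that the larger sample counteracts selection bias or gives generalizability.

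The cost is text and one short calculation, with no more women or clinics. The downside is that the stated power and the strength of the conclusion become less favourable. Only several clinics per arm, or randomising women within clinics, would separate clinic from intervention, and that would be a different study.

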- Information bias in chart review will be controlled by training of staff involved in data collection. Missing information
- Loss to follow up – a retention plan will be place to send clinic appointment reminders by sms or whatsapp, telephone calls in the case of missed visits and occasionally home visits when deemed necessary.
- Laboratory sample measurements will be performed by a certified laboratory.
- External -The larger proposed sample size will allow for external validity / generalizability.

1. List of Variables to be measured and schedule of evaluations

| CVD risk factors | Intervention Arm  (at main study PROMOTE scheduled visits)  Year 1(0+6m), Year 2(12+18m), Year 3(24+30m), Final study Visit (36m) | Control Arm | |
| --- | --- | --- | --- |
|  |  | **Year 1, 2, 3 (not including end of study visit) | Year 3 (end of study-36months) |
| Non-modifiable | Age (Categories in 5 year) | Age (Categories in 5 year) | Age (Categories in 5 year) |
|  | Race (A, I, W, C, O) | Race (A, I, W, C, O) | Race (A, I, W, C, O) |
|  | Family history of CVD in first degree relatives |  | Family history of CVD in first degree relatives |
| Modifiable | Smoking (Current, Never, Past) |  | Smoking (Current, Never, Past) |
|  | Unhealthy Diet |  | Unhealthy Diet |
|  | Exercise (minutes per week) |  | Exercise (minutes per week) |
|  | ART duration in years | ART duration in years | ART duration in years |
|  | ARV regimen | ARV regimen | ARV regimen |
|  | Viral load | Viral load | Viral load |
|  | CD4 count | CD4 count | CD4 count |
|  | BMI (6monthly) | BMI (6monthly) | BMI |
|  | Waist Circumference (6 monthly) |  | Waist Circumference |
|  | Systolic BP (6monthly) | Systolic BP | Systolic BP |
|  | Pulse (6monthly) |  | Pulse |
|  | Fasting Glucose (annual) |  | Fasting Glucose |
|  | Fasting Lipogram (annual) | Fasting Lipogram | Fasting Lipogram |
|  | hsCRP (annual) |  | hsCRP |
|  | Urine Microalbumin (annual) |  | Urine Microalbumin |
|  | *Carotid intima media thickness |  | Carotid intima media thickness |
|  | CVD risk % by Framingham |  | CVD risk % by Framingham |
|  | CVD risk % by DAD |  | CVD risk % by DAD |
|  | CVD risk % by WHO/ISH |  | CVD risk % by WHO/ISH |

*Only at year 3 in women aged over 40 years **Data collection through chart review

1. Plan for Data collection

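### If final values are compared, the tests named for continuous outcomes let an entry difference in BMI or systolic BP between two unrandomised clinics pass as a WHO PEN effect

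*Protocol*

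**What the plan says.** All references are to the protocol, Research design and methods, Overview, unless stated otherwise.

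- **Design.** The study is a "prospective two-arm, quasi-experimental design comparing a primary health care intervention plan with usual care". On sampling: "Method of selection will be via convenience sampling". The arms are "an intervention arm of 200 women co-enrolled in the PROMOTE study" and "a control arm of 200 women receiving HIV care at the PHC".
- **Comparability.** The validity section relies on matching: "careful matching between cohorts by age category and by duration of ART aims to counteract the potential for selection bias". BMI and blood pressure are not matching factors.
- **Tests.** Under analytic statistics: "The continuous variables will be compared by use of t-tests or Wilcoxon rank sum tests". No time point is given, and neither change from entry nor an entry covariate is mentioned.
- **Regression.** Logistic regression is named for predictors of cardiovascular disease and of carotid atherosclerosis. The confounder section adds a multivariate analysis whose type is misspelt. The confounders it lists are enrolment in a controlled study and CD4 count at ART start.
- **Available data.** The intervention schedule includes month 0, and its blood pressure row begins "Systolic BP (6monthly". In controls, BMI and systolic BP appear in the chart-review column for years 1 to 3 and again at the final visit. For the control arm: "Following informed consent, data will be collected from the participants ARV clinic medical chart as per the data collection tool". Chart review then repeats every six months, and the study itself measures controls only at the final visit.

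**The concern.** Modifying risk factors is a primary objective and weight control is a named part of the intervention, so BMI and systolic BP are core outcomes. One arm is an established research cohort and the other comes from a public clinic. Nothing in the selection makes them alike on BMI or blood pressure, and the protocol itself expects them to differ in other respects.

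A woman's entry BMI will usually predict her month-36 BMI strongly. A two-sample test on final values has no place for it. A gap that was there before the intervention and persists would then count as an effect, or would mask one. Even with balanced arms, the test would forgo precision that scheduled data could supply.

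**Working it through.** **The protocol's own figure.** The only sample-size figure is 132 per arm for metabolic syndrome, a binary outcome. For 30% v 15%, two-sided 5%, 80% power (the protocol states neither alpha nor sidedness):

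n = [1.96 × √(2 × 0.225 × 0.775) + 0.8416 × √(0.30 × 0.70 + 0.15 × 0.85)]² / 0.15² = 121, or 134 with continuity correction.

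That is close to 132. The figure does not involve BMI or BP, so this point does not alter it.

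**Inputs**

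| Input | Value | Source |
|---|---|---|
| Completers per arm | 200 × 0.9 = 180 | protocol: 200 per arm, 10% loss |
| BMI SD | 6.5 kg/m2 | assumed |
| BMI correlation r, entry to month 36 | 0.8–0.9 | assumed |
| Systolic BP SD; r | 16 mmHg; 0.5–0.6 | assumed |
| Entry gap d | 1.0 or 1.5 kg/m2 | assumed |
| Test level | 5% two-sided | assumed |

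**Step 1: unadjusted comparison of final BMI, no true effect.**
SE = 6.5 × √(2/180) = 0.685. The rejection rate is 1 − Φ(1.96 − b/SE) + Φ(−1.96 − b/SE), where b is the gap left at month 36.

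- Whole gap persists (b = d): for d = 1.0, b/SE = 1.46 and the rate is 31%. For d = 1.5, b/SE = 2.19 and the rate is 59%.
- Gap shrinks towards the mean (b = r × d): for d = 1.0, b = 0.8–0.9 and the rate is 21–26%. For d = 1.5 it is 42–50%.

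**Step 2: same setting, entry BMI as covariate.**
SE = 0.685 × √(1 − r²) = 0.411 (r = 0.8) or 0.299 (r = 0.9).

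- Whole gap persists: the remaining bias is (1 − r) × d. For d = 1.0 this is 0.20 or 0.10, giving 8% or 6%. For d = 1.5 it is 0.30 or 0.15, giving 11% or 8%.
- Gap shrinks to r × d: no bias remains and the rate is 5%.

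**Step 3: precision with balanced arms.** Detectable difference at 80% power = 2.80 × SD × √(1 − r²) × √(2/180).

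- BMI: 1.92 kg/m2 unadjusted; 1.15 (r = 0.8) or 0.84 (r = 0.9) adjusted.
- Systolic BP: 4.7 mmHg unadjusted; 4.1 (r = 0.5) or 3.8 (r = 0.6) adjusted.

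**Step 4: the risk in adjusting.** Control entry readings come from charts and control final readings from the study. Suppose the arms are truly balanced with no effect, but control chart BMI is off by 0.5 kg/m2 (assumed).

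- Covariate model: bias r × 0.5 = 0.40 or 0.45. Divided by 0.411 or 0.299, this gives 16% or 33% rejection.
- Change from entry: SE = 6.5 × √(2(1 − r)) × √(2/180) = 0.433 or 0.306. With bias 0.5, this gives 21% or 37%.
- Final-value t-test: 5%.

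**Check in SD units.** With 200 per arm, an entry gap of 0.2 SD and r from 0.5 to 0.9, the final gap is 0.10–0.18 SD and the unadjusted test rejects in 17–44% of null studies.

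**The case against.** Much of the case on the other side stands.

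- **The protocol does not specify a month-36 test.** A reader might infer that an unadjusted final-value comparison is fixed. The sentence gives no time point, and a t-test on changes would fit it and would use the entry value. That detail could also sit in an analysis plan. The false-positive rates therefore apply only if final values are compared.
- **Adjustment is promised.** It would be wrong to say that confounding is ignored. But the promised analysis appears to be logistic, which does not serve a continuous BMI or BP comparison, and entry BMI and BP are not among the listed confounders. This softens the point without answering it.
- **Entry values are not assured in every control.** The control column is headed by years, with no month 0, and its systolic BP cell lacks the six-monthly label. The literature review says only that vital signs are usually taken in HIV clinics, and that national guidelines make no BP screening recommendation in ART follow-up. Nor are BMI and BP the only such variables: the fasting lipogram also has a control chart cell, although the review says lipids are drawn only for women who need a protease inhibitor.
- **Adjustment brings its own risk.** Month 36 is the only time at which both arms are measured by the study. Step 4 shows that a modest chart offset could cost as much as the confounding being removed.

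**Conclusion.** The point holds in conditional form. The protocol names only two-sample tests for continuous outcomes in an unrandomised comparison, and gives the entry values of BMI and systolic BP no place in it. If final values are compared, an assumed 1.0 kg/m2 entry gap produces about 21–31% false positives. With adjustment the rate is 6–8% if the gap persists whole, and 5% if it shrinks by the factor r.

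The SDs, correlations, entry gap and chart offset are all assumptions, because the protocol gives none of them. The direction does not depend on their exact values; the size does. Two stronger inferences are not supported: that the study is committed to reading any entry gap as an effect, and that covariate adjustment would cure the problem. Adjustment reduces confounding but cannot remove it, and unmeasured differences between the clinics would remain. The stated sample size is unaffected.

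**What to change.** 1. For BMI and systolic BP, make the between-arm comparison a linear regression of the month-36 value on arm, entry value of the same variable, age and ART duration. Define entry as month 0 in the intervention arm and the chart reading nearest consent in controls.
2. Add entry BMI and entry systolic BP to the multivariable model for metabolic syndrome.
3. Report the unadjusted month-36 comparison and the change from entry as sensitivity analyses, because the control measurement source switches from chart to study.
4. Where a control chart holds a routine clinic reading near month 36, compare it with the study reading to look for a source shift. The chart-review column excludes the end-of-study visit, so this reading is not scheduled. The ethics section places the final control visit within a routine clinic visit, so a reading may exist for some women.

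**Cost.** Items 1 to 3 change analysis wording only; item 4 needs some extra chart extraction. Some control entry values will be missing and need imputation. A systematic chart offset would bias the adjusted estimate, so the three comparisons should be shown together and any disagreement explained.

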## Measurements of subclinical atherosclerosis

There is an increased prevalence of subclinical atherosclerosis in HIV infected people compared to HIV uninfected([48](#_ENREF_48)). Measurement of carotid intima media thickness (CIMT) by ultrasound is a non-invasive method of detecting subclinical atherosclerosis. In a local study of predominantly women, there was a 12% prevalence of subclinical atherosclerosis (CIMT >0.78 mm) which was associated with traditional risk factors of CVD rather than HIV-specific factors ([49](#_ENREF_49)).

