|  | BMI | WC | Fasting lipogram | Systolic BP | Fasting  Glucose | Urine microalbumin | hsCRP | Carotid initima medial thickness |
| --- | --- | --- | --- | --- | --- | --- | --- | --- |
| Age | x | x | x | x | x | X | x | X |
| Family History  of CVD | x | x | x | x | x | X | x | X |
| Tobacco use | x | x | x | x | x | X | x | X |
| Diet | x | x | x | x | x | X | x | X |
| Exercise | x | x | x | x | x | X | x | X |
| ART regimen | x | x | x | x | x | X | x | X |
| ART duration | x | x | x | x | x | X | x | X |
| VL | x | x | x | x | x | X | x | X |
| CD4 | x | x | x | x | x | X | x | X |
| BMI |  |  | x | x | X | X | x | X |
| WC |  |  | x | x | X | X | x | X |
| Fasting Lipogram |  |  |  | x | X | X | x | X |
| Systolic BP |  |  |  |  | X | X | x | X |
| Fasting Glucose |  |  |  |  |  | X | x | X |
| U-microalbumin |  |  |  |  |  |  | x | X |
| hsCRP |  |  |  |  |  |  |  | X |
| CVD risk % by Framingham |  |  |  |  |  |  |  | X |
| CVD risk % by DAD |  |  |  |  |  |  |  | X |
| CVD risk % by WHO/ISH |  |  |  |  |  |  |  | X |

1. Calculate cardiovascular risk as per WHO –ISH, DAD and Framingham, annually in intervention group and in the control group at year 3 and compare short term outcomes (presence of subclinical atherosclerosis by means of CMIT, presence of stroke, MI, angina -ischaemic heart disease)

1. Intervention:

**DIETARY CHANGES:** All individuals encouraged to reduce daily salt intake by at least one third and, if possible, to <5 g per day, to eat at least 400 g a day of a range of fruits and vegetables as well as whole grains and pulses and to reduce total fat and saturated fat intake

**PHYSICAL ACTIVITY:** All individuals encourage to do at least 30 minutes of moderate physical activity (e.g. brisk walking) a day, through leisure time, daily tasks and work-related physical activity.

**WEIGHT CONTROL:** All individuals who are overweight or obese should be encouraged to lose weight through a combination of a reduced-energy diet and increased physical activity

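### Primary objective 2: the only model named for CIMT is a logistic regression on a yes/no result in an unsized over-40 subset; continuous CIMT from the same scans would retain far more information

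*Protocol*

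**What the plan says.** Primary objective 2 (Protocol, Specific Objectives) compares three risk scores (WHO/ISH, DAD and Framingham) with short-term outcomes in women over 40. The outcomes are subclinical atherosclerosis on CIMT, stroke, myocardial infarction and angina.

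- **Scan.** The footnote to the schedule of evaluations (Overview) places CIMT "Only at year 3 in women aged over 40 years".
- **Models.** Under Statistical methods, "Logistic regression will be applied to identify predictors of cardiovascular disease between the two arms", and also "between those participants who exhibit atherosclerosis by carotid intima thickness" and those who do not. The same list plans t-tests or Wilcoxon tests for continuous variables and chi-square or Fisher tests for categorical ones. Multivariable adjustment is planned under the list of possible confounders.
- **Cut-off and prevalence.** Both appear only in the literature review, where in a local study "there was a 12% prevalence of subclinical atherosclerosis (CIMT >0.78 mm".
- **Timing of scores.** They are calculated "annually in intervention group and in the control group at year 3 and compare short term outcomes". The schedule gives both arms all three scores at 36 months.
- **Size.** The plan enrols "400 HIV-infected women consisting of an intervention arm of 200 women" and an equal control arm. The only calculation starts "With a 20-30% estimated prevalence of metabolic syndrome in people living with HIV" and concludes that "132 participants per arm would allow for 80% power". It does not address women over 40, CIMT or clinical events.

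**The concern.** CIMT is a continuous measurement taken once, in a part of the cohort whose size is not given. Reducing it to present or absent before modelling discards information where there is least to spare, and the few positive scans limit any adjustment to one or two covariates. The companion model for clinical cardiovascular disease has a similar shortage: women enter at 18-49 and are followed for three years, so events are probably scarce. In addition, the control arm's score is taken at the visit where CIMT is measured, and after any clinical event, so the word predictors claims more than that arm can show. At stake is a primary objective that could end with wide, inconclusive odds ratios, or with a same-visit association reported as predictive performance.

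**Working it through.** **The plan's own figure.** With 30% versus 15%, two-sided alpha 0.05 (assumed; not stated) and 80% power:

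n = [1.96·√(2·0.225·0.775) + 0.842·√(0.30·0.70 + 0.15·0.85)]² / 0.15² = 120.5, so 121 per arm, or 134 with continuity correction.

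The stated 132 is close to this, but only at that corner of the stated ranges (20% versus 10% needs 199 uncorrected). It concerns metabolic syndrome in all women and gives no support to objective 2.

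**Inputs for objective 2**
- 400 women and a 10% allowance for loss (Sampling): 360 completers.
- 12% with positive CIMT (literature review).
- Share over 40: not given; assumed 20-50%.
- Score-CIMT correlation r: not given; assumed 0.3.
- Three-year risk of stroke, infarction or angina: not given; assumed 0.25-3%.

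**Positive scans.** Cases = 360 × share × 0.12.
- 20%: 72 scans, 8.6 cases.
- 30%: 108 scans, 13.0 cases.
- 50%: 180 scans, 21.6 cases.

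At the rule of thumb of 10 cases per predictor, that supports 0.9-2.2 predictors. A model with one score and nothing else needs 10/0.12, about 84 women over 40.

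**Information kept after the cut.** For a normal variable cut at its upper fraction p, the share kept is φ(z)²/[p(1−p)]. At p = 0.12, z = 1.175 and φ(z) = 0.2000, so 0.0400/0.1056 = 0.379. A correlation of 0.30 shrinks by √0.379 = 0.616 to 0.185.

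**Power** (Fisher z, two-sided 0.05): Φ(atanh(r)·√(n−3) − 1.96), with atanh(0.30) = 0.3095 and atanh(0.185) = 0.187.

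| Women scanned | Continuous CIMT | Dichotomised |
|---|---|---|
| 72 | 73% | 34% |
| 108 | 89% | 48% |
| 180 | 98% | 70% |

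Simulating a one-predictor logistic regression (4,000 data sets, likelihood-ratio test) gave 36%, 49% and 72% for the dichotomised column, so the approximation is adequate.

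**Sensitivity to prevalence.** If 20% or 30% of women over 40 were positive, the information kept would be 49% or 58%. The loss shrinks but remains.

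**Clinical events.** Events = N × risk. In 400 women: 400 × 0.0025 = 1 to 400 × 0.03 = 12. In 120 women over 40 (30% of 400): 0.3 to 3.6.

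**Timing.** Intervention scores are annual. Control scores exist only at month 36, the CIMT visit. The one score common to both arms is concurrent with the scan.

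**The case against.** The strongest reply has five parts.

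1. *The logistic sentence is not tied to objective 2*, and t-tests or Wilcoxon tests could compare scores between CIMT groups. This is fair, but such tests still split CIMT into two groups and lose the same information. Logistic regression remains the only model named for CIMT.
2. *The objective itself is worded as presence of atherosclerosis.* This stands, and is why the yes/no result should be kept as secondary or descriptive. Moving to millimetres changes the scale of the main result.
3. *A reader might infer a 19-predictor model with about one case or fewer per predictor.* The documents do not support that. The 19 rows marked against CIMT belong to a list of associations, crossed with other outcomes too, and the scores stand beside their own components. No joint model is specified.
4. *A reader might infer that the different score times make the models inestimable, or that entry scores in one arm will be pooled with year-3 scores in the other.* Neither follows. A month-36 score exists in both arms, and timing bears only on the claim of prediction.
5. *The sizes rest on assumptions.* This also stands. The age share, the correlation and the event rate are not in the documents, and the 12% comes from a study whose age range is not given. Clinical outcomes are worded as presence and prior disease is not excluded, so a count of new events may be too low.

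A cut-off, covariate list or score time point may properly sit in an analysis plan that is not shown. Their absence is not the point. The point is the weaker method that the Protocol does name.

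**Conclusion.** The point holds as a low-cost improvement to a stated method. The Protocol names logistic regression on a yes/no CIMT for a subset that it has not sized. At its own 12% figure and an assumed 20-50% over 40, that means about 9-22 positive scans and room for one or two covariates. The cut keeps about 38% of the information, assuming roughly normal CIMT. At an assumed correlation of 0.3 it costs about 28-41 percentage points of power over 72-180 women. Clinical events are probably too few for an adjusted logistic model (1-12 in 400 women at the assumed risks, fewer over 40), but the documents give no rate and this is not certain. In the control arm the score-CIMT relation is cross-sectional. It does not follow that every planned model fails: a single-score logistic model is workable with about 84 or more women over 40, though with less power than the same scans allow.

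**What to change.** - Make the main CIMT analysis a linear regression of continuous CIMT (log-transformed if skewed) on each month-36 score, one score per model, using both arms, with arm and at most a few covariates.
- Keep presence of subclinical atherosclerosis as a descriptive or secondary result, and align the wording of objective 2 with this.
- Call the analysis cross-sectional.
- Report stroke, myocardial infarction and angina as counts with exact confidence intervals in place of the logistic model.
- State that objective 2 is estimation only, because the sample size covers only metabolic syndrome.

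The scans, visits and scores are unchanged; the cost is revised wording in the objective and the statistical methods. The downside is that the main result is in millimetres of CIMT and not an odds ratio, and that no predictor model for clinical cardiovascular disease is claimed.
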